## Abstract

**Background:**

Epileptic encephalopathy with electrical status epilepticus in sleep (ESES) is an epilepsy syndrome occurring almost exclusively in children, usually at an age between 4 and 12 years. It is characterised by abundant sleep-induced epileptic activity in the electroencephalogram (EEG) and by acquired cognitive and behavioural deficits. The goal of treatment is to prevent further decline or even improve cognitive functioning. Based on mostly small and retrospective studies, corticosteroids and clobazam are regarded by many clinicians as the most effective pharmacological treatments. This European multicentre randomised controlled trial is designed to compare the effects of corticosteroids and clobazam on cognitive functioning after 6 months. Secondary outcomes include cognitive functioning after 18 months, EEG abnormalities in sleep, safety and tolerability, and seizure frequency. We also aimed at investigating whether treatment response in epileptic encephalopathy with ESES can be predicted by measurement of inflammatory mediators and autoantibodies in serum.

**Methods:**

The pragmatic study will be performed in centres with expertise in the treatment of rare paediatric epilepsy syndromes across Europe. A total of 130 patients, 2 to 12 years of age, with epileptic encephalopathy with ESES will be enrolled and randomised in a 1:1 ratio to receive either corticosteroids (monthly intravenous methylprednisolone pulses or daily oral prednisolone) or oral clobazam for 6 months according to an open-label parallel-group design. Follow-up visits with clinical assessment, EEGs, and neuropsychological testing are scheduled for up to 18 months. Blood samples for cytokine and autoantibody testing are obtained before treatment and 8 months after treatment initiation.

**Discussion:**

The treatment of epileptic encephalopathy with ESES aims at improving cognitive outcome. This randomised controlled study will compare the most frequently used treatments, i.e. corticosteroids and clobazam. If the study proves superiority of one treatment over the other or identifies biomarkers of treatment response, results will guide clinicians in the early treatment of this severe epilepsy syndrome.

**Trial registration:**

ISRCTN, ISRCTN42686094. Registered on 24 May 2013.

The online version contains supplementary material available at 10.1186/s13063-020-04874-2.

## Background

Electrical status epilepticus in sleep (ESES) was initially described as a subclinical electroencephalographic (EEG) pattern of sleep-induced spikes and waves (SWs) in children, occupying 85–100% of slow wave sleep [1]. When bilateral ESES is associated with cognitive decline or behavioural disturbances, a diagnosis of encephalopathy with ESES can be made. The cognitive deficits are global (often referred to as continuous spikes and waves syndrome, CSWS) or confined to a specific cognitive domain (e.g. acquired aphasia or auditory agnosia in children with Landau-Kleffner syndrome, LKS) [2, 3]. These phenotypes are referred to as “typical ESES patients” [4, 5]. The exact incidence of the epileptic encephalopathy with ESES is unknown, but it is estimated to constitute 0.2–1.9% of paediatric epilepsy cases [5, 6].

ESES spectrum variants are increasingly recognised and include children with ESES and developmental delay but without arrest or regression of development [7]. Also, the spike wave index (SWI) threshold to diagnose ESES can be flexible, and can be < 85%, provided that the main feature of epileptic encephalopathy with ESES, i.e. occurrence of cognitive and behavioural deterioration associated with a striking enhancement of epileptic activity during NREM sleep, is demonstrated [8]. How ESES causes cognitive deficits and which factors determine cognitive outcome remain largely unknown. It has been suggested that ESES disrupts synaptic homeostasis, i.e. the balanced synaptic potentiation during daytime and synaptic downscaling in sleep, leading to an inefficient cerebral network [9]. Epileptic encephalopathy with ESES has been reported in patients with structural abnormalities (e.g. perinatal thalamic injury) [10, 11] and genetic disorders (e.g. a GRIN2A mutation) [12, 13], though in about half of the cases no clear cause is identified. Evidence is accumulating for a role of the immune system in patients with epilepsy [14]. In children with Landau-Kleffner syndrome, autoantibodies to central and peripheral myelin, cell nucleus, and blood vessels in sera and cerebrospinal fluid have been found [15]. In addition, in a previous study, we found that several cytokines were significantly higher in blood samples of patients with encephalopathy with ESES compared with healthy controls [16].

Whilst the EEG abnormalities characteristic of ESES generally resolve spontaneously during puberty, cognitive deficits often remain [17, 18]. Treatment during the active ESES phase may improve EEG abnormalities and daily functioning [19, 20]. In fact, successful early treatment (and thereby a shorter ESES duration) is associated with improvement of long-term cognitive outcome [18, 21]. However, the management of encephalopathy with ESES is often challenging and there is no consensus on which is the best initial treatment [22]. Moreover, no adequately powered randomised controlled trials have been performed in children with encephalopathy with ESES.

We recently performed a pooled analysis of 950 treatments in 575 cases with encephalopathy with ESES, reported in 112 articles. Conventional anti-epileptic drugs, often prescribed to control concomitantly occurring epileptic seizures, were generally not very effective in treating ESES and its associated cognitive deficits (improvement of EEG or cognition in 49%). Benzodiazepines and corticosteroids seemed to be more effective, with improvement in 68% and 81% of cases, respectively. However, in a subgroup analysis that included only consecutively assessed patients, a smaller proportion showed any improvement (34% with conventional anti-epileptic drugs, 59% with benzodiazepines, and 75% with corticosteroids). A subgroup of patients with a focal structural abnormality benefitted from epilepsy surgery. These results have to be interpreted with caution because most included studies were small, retrospective, and heterogeneous, and side effects were not considered [19].

Review articles on the treatment of encephalopathy with ESES concluded that no standard approach exists and mentioned high-dose benzodiazepines and (cortico) steroids as preferred options [5, 6, 23]. Among benzodiazepines, clobazam is often considered the most suitable although sedation and agitation are frequent side effects. Corticosteroids have been given in variable dosing regimens, and concerns for side effects such as weight gain and increased blood glucose may be a reason to consider them as a second-line option. All authors emphasise that the evidence guiding the treatment of encephalopathy with ESES is unsatisfactory, and therefore, a randomised controlled trial is urgently needed.

We hypothesise that, in comparison to treatment with clobazam, corticosteroids are more effective in improving cognitive performance and EEG abnormalities in children with encephalopathy with ESES. Based on previous studies, the difference in percentage of responders is estimated at around 25% [19]. The use of corticosteroids may be associated with more frequent or more severe side effects than clobazam.

In a multicentre randomised controlled trial with 1:1 allocation to corticosteroids and clobazam, we aim to assess whether one of the treatments is superior to the other. The following study objectives and hypotheses are addressed in a population of recently diagnosed patients with encephalopathy with ESES:

*Primary study objective*
To compare the effects of treatment with corticosteroids or clobazam on cognition at 6 months after start of the treatment.

*Secondary study objectives*
To compare the effects of treatment with corticosteroids or clobazam on sleep-induced epileptiform activity, measured as the spike wave index (SWI), in the patients’ sleep EEG.To compare the effects of treatment with corticosteroids or clobazam on the frequency of any concomitant seizures.To compare the side effects and tolerability of corticosteroids and clobazam.To compare the effects of treatment with corticosteroids and clobazam on subjective daily functioning, as measured with a visual analogue score (VAS).To assess demographic and disease-related biomarkers, including immunological biomarkers, as potential predictors of disease activity and response to treatment with corticosteroids or clobazam.

The study is conducted as a randomised open-label parallel-group controlled trial with 1:1 treatment allocation to clobazam and corticosteroid treatment arms and is aimed at proving superiority of one treatment over the other. The trial also uses a pragmatic approach, whereby participating investigators will be allowed to apply, within predetermined limits, the dosing schedules which they consider best according to their judgement and patient response. The same flexibility will also apply to the option of using i.v. versus oral steroids, which will be left to the discretion of the treating physicians.

## Methods

### Study setting

Study preparations have been initiated in 22 centres with expertise in the treatment of rare paediatric epilepsy syndromes across 12 European countries. Details of the participating centres can be found under the “Trial status” section at the end of this manuscript.

### Study population

The study will include 130 patients with encephalopathy with ESES, with typical or atypical presentation and symptoms, according to the following eligibility criteria. The overall duration of follow-up will be 18 months.

#### Inclusion criteria

Age at inclusion, 2 up to 12 years.A diagnosis within 6 months prior to enrolment (preferably as close to enrolment as possible) of either:
Bilateral sleep-induced epileptiform activity with an SWI > 85% in non-REM sleep and developmental delay, arrest, or regression (“typical epileptic encephalopathy with ESES”).Arrest or regression of development and bilateral sleep-induced epileptiform activity with an SWI > 50%, or unilateral sleep-induced epileptiform activity with an SWI > 85% in non-REM sleep (“atypical epileptic encephalopathy with ESES”).Regression of development and unilateral epileptiform activity with an SWI > 50% in non-REM sleep (“atypical epileptic encephalopathy with ESES”).No previous treatment with either corticosteroids or clobazam.No current treatment, nor treatment in the previous 3 months, with carbamazepine, oxcarbazepine, vigabatrin, tiagabine, gabapentin, and pregabalin. These drugs potentially increase the SWI during sleep and may cause an electrographic pattern fulfilling the criteria for ESES and subsequently worsen outcome in children with epileptic encephalopathy with ESES and may thereby influence treatment results. Therefore, inclusion of such cases with possible “treatment-induced ESES” is not desirable.Written informed consent by parents/legal representatives.

#### Exclusion criteria

Patients with an SWI during wakefulness of > 50%.Any condition that, in the investigator’s judgement, contraindicates the use of corticosteroids or clobazam, such as acute or chronic infectious disease (e.g. tuberculosis, HIV), immunodeficiency, severe osteopenia/osteoporosis, diabetes mellitus, Cushing syndrome, severe respiratory insufficiency, severe liver failure, or gastrointestinal ulcer.

### Informed consent

Parents/legal representatives of potentially eligible patients are informed by the treating doctor about the background, study design, and study procedures. A medical ethics committee-approved patient information leaflet describing the study background, aims, design, procedures, and timeline and highlighting any differences with standard care is provided to all parents/legal representatives. A leaflet version describing the study in basic language for the children above 6 years of age meeting their abilities to understand the content is available. Parents/legal representatives/patients have at least 7 days to consider participation, and their questions will be answered. Informed consent forms with approval for participation in the study, including the collection of blood samples and the storage of study data for a fixed period (depending on the standard per country, 15 years for the Netherlands), will be signed and filed. Study participants may withdraw from the trial anytime during the conduct of the study.

### Treatment

Patients will be enrolled by their treating physician/study doctor, who has no direct insight in the allocation mechanism of the randomisation module. Treatment is allocated according to an automatic online randomisation module with block randomisation stratified for centre to the two treatment regimens (1:1 ratio). The randomisation module was programmed by a data manager. The patients and treating physicians are not blinded for treatment allocation, as this was considered not feasible with two treatment arms that differ in their prescription form (in most centres, corticosteroids are given as intravenous monthly pulses, whilst clobazam is given as a tablet to be taken daily) and because the two treatments require different monitoring. The neuropsychological assessment and EEG assessment will be performed by personnel blinded for treatment:
Clobazam will be administered orally and increased to a dose of 0.5 mg/kg/day within 2 weeks. If well tolerated, dosage may be increased up to 1.2 mg/kg/day (given once daily, in the evening). Treatment with a dosage of at least 0.5 mg/kg/day will be continued for 6 months and thereafter will be either continued or tapered according to the treating physician’s preference. Clobazam is defined by active substance for this study. It is prescribed as tablets, and brand names include Frisium, Onfi, and Tapclob as well as generic products.Corticosteroids: either intravenous methylprednisolone or oral prednisolone will be used, depending on local experience and preference.Intravenous methylprednisolone will be given as monthly pulses. A dosage of 20 mg/kg will be given over 30 min once a day for 3 consecutive days, every 4 weeks, for a total period of 6 months with the intention to stop thereafter.Oral prednisolone will be administered at an initial dosage of 2 mg/kg/day (not exceeding 60 mg/day) for 1 month, followed in the 2nd through 6th month by a dosage between 1 and 2 mg/kg/day (not exceeding 60 mg/day), according to the treating physician’s judgement. Thereafter, prednisolone will be either continued or tapered according to the treating physician’s preference.

Treatment will be continued for at least 6 months, unless informed consent is withdrawn, the patient develops intolerable adverse effects, or further cognitive regression occurs, requiring an alternative intervention in the opinion of the treating physician. If cognitive regression is observed to continue after 3 months of treatment, according to the impression of the parents or physician, switching to the other treatment arm is allowed. In patients requiring switching to an alternative treatment, an EEG will be obtained before switching.

Drug adherence to oral treatment (oral clobazam or oral prednisolone) will be optimised and monitored by instructing patients to bring their empty packages of study medication to the hospital at every scheduled visit, together with completed drug intake diaries. In addition, for patients treated with clobazam, plasma levels will be measured in blood samples collected between 1 and 3 months after enrolment and between 3 and 6 months after enrolment. For intravenous methylprednisolone, adherence will be confirmed by recording drug administration at times of hospital admission for the monthly pulses.

Concomitant medication will be allowed as long as the patient fulfils the criteria for inclusion. However, changes in concomitant medications are discouraged during the first 6 months. After assessment of the primary endpoint at 6 months, subsequent treatment strategies will be left to the clinical judgement of the treating physician.

### Outcomes

The co-primary outcome measures at 6 months will be cognitive functioning, assessed with a full neuropsychological assessment (NPA):
Intelligence quotient (IQ), or developmental quotient (DQ), compared to baseline IQ/DQ. Improvement is defined as an increase by 10 IQ/DQ points.Cognitive sum score (as defined below). Improvement is defined as statistically significant when improved by at least 75% of the standard deviation (SD).

Secondary outcome measures at 6 and 18 months will include the following:
Changes in individual absolute test results, and IQ/DQ scores, compared to baseline.Changes in spike wave index (SWI) during non-REM sleep, compared with baseline SWI.Changes in seizure frequency assessed for all reported seizure types combined, with improvement being defined as at least 50% decrease as compared with baseline.Changes in subjective global daily functioning assessed with a visual analogue score (VAS) of − 5 to + 5 as compared with baseline.Safety and tolerability, as assessed by the occurrence of adverse events.Change in inflammatory markers post-treatment as compared to levels prior to treatment.Identification of autoantibodies as potential biomarkers of disease severity (TIQ, presence of developmental regression, arrest, or delay and SWI at baseline) and treatment efficacy.

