### Sleep EEG at baseline and after 1, 3, 6, and 18 months

The diagnosis of encephalopathy with ESES will have to be confirmed by whole-night EEG recording prior to randomisation. Depending on the logistics of the participating centres, either sleep-deprived EEGs of at least 1 h or whole-night recordings will be considered adequate for follow-up assessments. Technical requirements for the EEG recordings are specified in an appendix to the study protocol. Clinical neurophysiologists will be blinded to the type of treatment.

For each EEG, the spike wave index (SWI) will be calculated in an epoch of 10 min (600 s) duration, starting 5 min after alpha attenuation or after sleep had clinically commenced. The number of seconds containing epileptiform discharges is divided by the total number of seconds in the epoch (600) and multiplied by 100 to reflect the SWI as a percentage.

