### Data collection during follow-up

Epilepsy characteristics and information on neurodevelopment, other medical history, neurological examination, concomitant medications, possible treatment emergent adverse events, and sleep EEGs will be collected 1, 3, 6, and 18 months after start of treatment. Neuropsychological assessments will be repeated only after 6 and 18 months to minimise re-test bias. After 3 months, a brief assessment of cognitive performance is performed by the clinician to detect possible ongoing regression that may warrant a change of treatment. In the corticosteroid treatment group, additional safety and tolerability assessments will include monitoring of blood pressure, glucose, and protein in urine and weight monitoring once weekly plus additionally at any hospital visits (including admissions for methylprednisolone pulses, when applicable). In case of stress, high fever or illness managements in these situations will be left to treating physician and details will be recorded in eCRF.

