### Statistical analysis

The primary analyses will be performed according to the intention-to-treat principle. We will also perform (secondary) analyses in patients who have completed their assigned treatment for the period of 6 months.

Continuous outcomes will be presented with means and 95% confidence intervals. These outcomes will primarily be compared between the two treatment groups using a *t* test or Mann-Whitney *U* test depending on the distribution of the data (normal vs not normal). Categorical outcomes will be presented as proportions with 95% confidence intervals. These outcomes will primarily be compared between the two treatment groups using Fisher’s exact test. Rates of (serious) adverse events will be compared in terms of risk ratios with corresponding 95% confidence intervals. We will also identify the proportion of patients that continue on the initially allocated treatment throughout the entire study period, and analyse possible predictors for discontinuation.

Although the stratified randomisation procedure intends to create two groups with equal patient characteristics, it is known that in randomised trials of < 1000 patients, there still is a risk of bias by chance [25]. Adjusted analyses are often performed to reduce the influence of the possible differences between the two treatment arms [26]. Therefore, possible predictors of treatment outcome (i.e. known prognostic factors) will be included in a multivariate logistic/linear regression model. These prognostic factors are as follows: age at ESES recording, time interval between ESES recording and inclusion, IQ levels and cognitive sum scores at enrolment, number of drugs administered before enrolment, and aetiology (unknown, structural, metabolic, genetic, immune, infectious). We will also include cytokine and autoantibody profiles as possible predictors.

The prospective design and structured follow-up schedule should minimise the amount of missing data. However, to account for possible influence of missing data, we will perform a sensitivity analysis using multiple imputation methods [27].

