## Discussion

Encephalopathy with ESES is characterised by sleep-induced epileptic activity accompanied by acquired cognitive deficits. Treatment aims at improving cognitive functioning. Current evidence regarding treatment efficacy is limited to mostly retrospective case series and indicates that conventional anti-epileptic drugs are often not effective, and that benzodiazepines and corticosteroids can provide greater benefit in improving cognition and EEG abnormalities. In patients with an operable structural lesion, surgery seems to be the most effective treatment.

The current study aims at comparing the efficacy of corticosteroids versus clobazam in improving cognitive functioning in children with ESES. The co-primary outcomes are cognitive functioning, as measured with total IQ scores and cognitive sum scores after 6 months. Secondary outcomes include cognitive functioning after 18 months, the spike wave index after 6 and 18 months, safety and tolerability, subjective assessment of daily functioning, and whether disease severity and treatment effect can be predicted, among other characteristics, by measuring serum levels of cytokines or autoantibodies.

The conduct of this multinational multicentre study in the rare population of patients with ESES is challenging for several reasons. Firstly, the differences in legislation and regulations between the involved countries and the requirement of obtaining ethics committee and competent authority approval for each of these countries are difficult and time-consuming. Secondly, although clobazam and corticosteroids are widely prescribed in regular clinical care, in some countries, labelling of the study drugs for this specific indication was considered to be required and posed a logistical challenge. Thirdly, each centre had their own requirements in terms of clinical trial contracts and this resulted in numerous email and telephone discussions between legal representatives. Altogether, these challenges caused considerable delay of the initiation of study at participating centres and resulted in withdrawal of several centres.

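### SWI is measured at months 1, 3, 6 and 18, but the stated main month-6 comparison is an unadjusted single-visit test that leaves out children without a month-6 EEG and uses neither their earlier SWI nor baseline SWI as a covariate

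*Protocol article*

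**What the plan says.** **Measurement.** The EEG section of the protocol article is titled "Sleep EEG at baseline and after 1, 3, 6, and 18 months", and Data collection during follow-up agrees: "sleep EEGs will be collected 1, 3, 6, and 18 months after start of treatment". SWI is derived every time: "For each EEG, the spike wave index (SWI) will be calculated in an epoch of 10 min (600 s) duration".

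**Outcome.** Under Outcomes, the list headed "Secondary outcome measures at 6 and 18 months will include the following" contains "Changes in spike wave index (SWI) during non-REM sleep, compared with baseline SWI". The Discussion repeats the times: "the spike wave index after 6 and 18 months". The objective in the Background, to compare the treatments "on sleep-induced epileptiform activity, measured as the spike wave index (SWI), in the patients’ sleep EEG", gives no time point.

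**Analysis.** For continuous outcomes, Statistical analysis says "These outcomes will primarily be compared between the two treatment groups using a" t test or a Mann-Whitney U test, depending on the distribution. An adjusted regression is added. Its factors are age at ESES recording, interval to inclusion, enrolment IQ and cognitive sum score, number of earlier drugs, aetiology, and cytokine and autoantibody profiles. Baseline SWI is not listed. Missing data are addressed by multiple imputation as a sensitivity analysis. The section on recruitment and retention says that data gathered before discontinuation will still be analysed, and that children who switch arms and stay in follow-up remain in the intention-to-treat analysis.

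**The concern.** SWI is the first-listed secondary objective and part of the trial's hypothesis. The stated main test compares one visit at a time, which has three consequences.

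- A child with EEGs at months 1 and 3 but none at month 6 contributes nothing to the main month-6 SWI result. If such children differ in early SWI, that result can be biased.
- The article promises to analyse data collected before discontinuation, but names no SWI analysis that would take in months 1 and 3.
- Baseline SWI enters only through subtraction. A change score is usually less precise than adjustment for baseline.

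At stake is the accuracy of a key secondary result in a rare disease where recruitment is already slower than expected.

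**Working it through.** **1. Recordings.** Four scheduled follow-up EEGs × 130 children = 520. Months 1 and 3 account for 2 × 130 = 260. Half of the scheduled follow-up SWI values thus fall outside the listed outcome times.

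**2. The plan's own figure.** Sample size calculation gives 65 per arm and a detectable standardised difference of around 0.5 at 80% power and two-sided 5%. Detectable d = (1.960 + 0.842) × √(2/65) = 0.491. Power at d = 0.5 is Φ(0.5/√(2/65) − 1.960) = Φ(0.890) = 81.3%. The figure reproduces.

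**3. With the plan's 10% dropout.** 65 × 0.9 = 58.5 per arm. Power at d = 0.5 is Φ(0.5/√(2/58.5) − 1.960) = 77.2%, and detectable d is 0.518.

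**4. What months 1 and 3 add to the month-6 contrast.** The documents give no correlation between visits. Assume an equal correlation ρ of 0.3 to 0.9. If the early visits explain a share p of the remaining month-6 variance and a fraction f lacks month 6, the effective number per arm is 65 / [p + (1 − p)/(1 − f)].
- With baseline adjustment, p = [3ρ²/(1 + 2ρ) − ρ²]/(1 − ρ²). For ρ = 0.5, p = (0.375 − 0.25)/0.75 = 0.167, giving 65/1.0926 = 59.5.
- With change scores, p = 1/3 for any ρ, giving 65/1.0741 = 60.5.
- Over the whole range the effective number is 59.0 to 60.5 per arm and power is 77.5% to 78.5%, a gain of about 0.4 to 1.4 percentage points. Simulated variance ratios agree, at 1.0 to 1.1.

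**5. What baseline adjustment adds.** Let k be the baseline SD divided by the month-6 SD. The variance of the change-score comparison relative to the baseline-adjusted one is (1 + k² − 2ρk)/(1 − ρ²).

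| ρ (baseline with month 6) | k = 1 | k = 0.5 |
|---|---|---|
| 0.2 | 1.67 | 1.09 |
| 0.3 | 1.54 | 1.04 |
| 0.5 | 1.33 | 1.00 |
| 0.7 | 1.18 | 1.08 |

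The upper end, combined with step 4, is 1.67 × 1.1 ≈ 1.8. The gain largely disappears when baseline SWI varies little, which is plausible because entry requires SWI above 50% or 85%.

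**6. Bias.** Suppose loss at month 6 depends on month-3 SWI. With equal SDs, the slope of the change score on month-3 SWI within an arm is r(3,6) − r(0,3).
- If all correlations are equal the slope is zero, and the planned change-score test is essentially unbiased.
- If baseline correlates less with follow-up than the follow-ups do with each other, the slope is positive and the estimate shrinks.

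Simulations assumed 65 per arm, a true difference of 15 points and, typically, SD 30.
- With about 13% to 23% missing, the planned test gave about 14.0 to 15.2 and the repeated-measures model stayed near 15.
- Harsher settings (baseline correlation 0.2 to 0.5, follow-up correlation 0.5 to 0.7, up to 20% missing) took the planned test as low as 13.2.
- Adjusting for baseline alone, on available month-6 values, did not cure this: 14.35 and 14.02 at 10% missing, 13.83 and 13.20 at 20%. The repeated-measures model gave 14.84 to 15.09.

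The two parts of the model therefore do different work. Baseline SWI brings the precision, and the early visits bring the protection against bias.

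**The case against.** The strongest reply is that this is a condensed article. A longitudinal model for a secondary outcome could sit in an analysis plan that is not shown, and neither the test sentence nor the open-ended outcome list excludes further analyses. Measuring at four visits and naming two as outcomes is ordinary, limits multiplicity, and matches the two follow-up neuropsychological assessments. This stands to the extent that the article contains no error or contradiction. It does not remove the point, because the article does state the outcome times, the main test, the covariates and the role of imputation, and a better main analysis is available.

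Other parts of the reply also stand.

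- A reader might infer that the month-1 and month-3 EEGs add nothing. The documents do not say so. SWI is calculated from them, they may serve clinical follow-up, and the unspecified imputation model could use them.
- A reader might infer that children without a month-6 EEG drop out of the analysis altogether. They leave only the unimputed comparison, and switchers who stay in follow-up are kept.
- Loss driven by early SWI is an assumption. Treatment section reasons for stopping are withdrawn consent, adverse effects and cognitive regression, not SWI.
- A bias of 1 point is small beside a standard error of about 30 × √(2/58.5) = 5.5 points.
- Speed of action is not a stated objective, so the plan cannot be faulted for not showing it.

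**Conclusion.** The point holds as a modest improvement to a secondary analysis. As stated, the main month-6 SWI comparison leaves out children without that EEG, gives their earlier SWI no named role, and does not adjust for baseline SWI; imputation is only a sensitivity analysis.

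The size is about 0 to 1 point of bias on a 15-point effect in most settings, conditional on loss depending on early SWI, and up to 1.8 points (15 − 13.2) in the harshest simulated setting with twice the planned dropout. The variance gain runs from none to about 1.8-fold, mainly through baseline SWI. The SDs, correlations, 15-point effect and loss mechanism are all assumptions; the documents give none of them. The protection against bias also requires that loss be explained by the SWI values already observed.

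A reader might infer a much larger gain by averaging months 1, 3 and 6. Under equal correlation the variance of the averaged change is [4(1 − ρ)/3]/[2(1 − ρ)] = 0.67 of the single-visit change, and power would rise to about 91% at 58.5 per arm if the effect were equal at all three visits. That is a different estimand from the one the article lists, so it does not measure what the planned month-6 comparison loses.

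**What to change.** State that the main month-6 SWI comparison is the month-6 treatment contrast from a mixed model for repeated measures on months 1, 3 and 6, with baseline SWI, arm, visit, arm-by-visit interaction and an unstructured covariance. Report the month-1 and month-3 contrasts from the same model as supportive. Keep the Mann-Whitney test at month 6 as a sensitivity analysis, because SWI is bounded at 100%. If multiple imputation is retained, state that its model includes baseline, month-1 and month-3 SWI.

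The cost is analysis wording only: the recordings are already scheduled and the month-6 outcome is unchanged. The small downside is reliance on a normal model for a bounded score, which the rank-based analysis checks. A child with no EEG after baseline still contributes no follow-up information.
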